## Abstract

**Introduction:**

Olfactory impairment is common in glioblastoma and has been associated with unfavorable overall survival. However, prior studies were limited by imbalances in key prognostic factors and the absence of longitudinal olfactory assessments to evaluate treatment-related neurotoxicity. The aim of the study is to determine whether olfactory function serves as an independent prognostic marker for survival, neurocognitive outcomes, and quality of life in glioblastoma.

**Methods:**

Prospective, multicenter cohort study enrolling 64 glioblastoma patients and 64 matched healthy controls. Patients are stratified by extent of resection, O6-Methylguanine-DNA Methyltransferase promoter methylation, radiographic involvement of olfactory regions, baseline olfactory status, age, and Karnofsky performance status. Olfactory function is assessed serially using Sniffin’ Sticks (identification and threshold tests) from diagnosis through treatment. Coronal T2- and T1-weighted MRI scans are reviewed independently by two blinded neuroradiologists to detect olfactory region involvement. Neurocognitive testing, psychosocial screening, and quality of life assessments are conducted at defined intervals. Next-generation sequencing from tumor tissue is employed to explore molecular underpinnings of hyposmia. Blood samples are collected in every study visit for potential parallel translational studies.

**Perspective:**

This is the first longitudinal study evaluating olfactory function as a prognostic biomarker in glioblastoma. Findings may inform risk stratification, guide neuroprotective strategies, and improve survivorship care.

**Trial registration:**

ClinicalTrials.gov, NCT06954636, date of registration 04-16-2025 (retrospectively registered); https://clinicaltrials.gov/study/NCT06954636?cond=glioblastoma&intr=olfactory&rank=1.

## Introduction

Glioblastoma is the most common malignant brain tumor in humans, the median overall survival is between 12 and 48 months [9, 18]. Tumor therapy primarily involves maximum safe surgical resection, radiotherapy, chemotherapy, and Tumor Treating Fields. Olfactory dysfunction is widely acknowledged as a symptom of various neurological disorders, including Parkinson's disease and Alzheimer's disease [19]. The significance of olfactory function in glioblastoma remains poorly understood. Possible explanations for olfactory dysfunction in glioblastoma include microscopic infiltration of the olfactory centers by tumor cells, tumor cell migration from the subventricular zone (SVZ) via the rostral migratory pathway (RMS) toward the olfactory bulbs, the SVZ itself as a source of cellular supply during tumor development, and the side effects of tumor-specific therapies [5–7, 12, 15].

In a previous study, we demonstrated that patients with glioblastoma are significantly more prone to olfactory dysfunction than a control group of patients with non-tumorous neurological diseases not primarily associated with smell impairment [12]. The study demonstrated the prognostic relevance of an olfactory dysfunction in glioblastoma patients regardless of the olfactory tract affection by the tumor. We studied 122 patients (73 glioblastoma patients and 49 controls). All were tested at various time points using the Sniffin Sticks screening test—a 12-odor test where participants identify each odor from four predefined options. Normosmia was defined as a Sniffin Sticks score (SSC) of 9.9 or higher [10]. Patients scoring below 10 were classified as the hyposmia group (HG), while those scoring 10 or higher were classified as the normosmia group (NG) [12]. After the initial examination, 34 glioblastoma patients were assigned to the HG and 39 to the NG. O6-Methylguanine-DNA Methyltransferase (MGMT) promoter methylation, age, sex, Karnofsky performance status (KPS), tumor histology, and extent of resection did not differ significantly between the two groups. Glioblastoma patients scored significantly lower on the smell test than controls (mean SSC 8.9 vs. 9.9, *p* = 0.003). Even patients tested before chemotherapy or radiotherapy onset performed worse than controls (mean SSC 8.2 vs. 9.9, *p* = 0.001). MRI was used to determine if tumor growth affected primary olfactory centers (ethmoid bone, olfactory groove, or temporomesial structures like the posterior orbitofrontal cortex, uncus, anterior parahippocampal gyrus, entorhinal area, insula, or amygdala). The median overall survival (OS) of the cohort was 28.1 months, and the median progression-free survival (PFS) was 14 months. Patients in the HG had worse OS (20.9 vs. 40.6 months, *p* = 0.035) and PFS (9 vs. 19 months, *p* = 0.022) compared to NG.

In our previous study, longitudinal analysis was hampered by limited re-examinations during follow-up (n = 32). Only some patients were assessed before chemoradiotherapy (n = 15), restricting our ability to evaluate neurotoxicity from radio- and chemotherapy. Additionally, the HG was older, had lower MGMT promoter methylation rates, and a lower KPS than the normosmia group—differences that, though not statistically significant, are crucial in ensuring that the groups were not distributed exactly equally, which led to criticism from readership.

Therefore, this prospective, multicenter study aims to determine whether olfactory dysfunction can serve as an independent prognostic marker for glioblastoma outcomes when controlling for known confounders and following patients longitudinally. The hypothesis is that the disturbance of olfactory function is intrinsically caused by the disease itself and not by external factors such as radiochemotherapy or tumor infiltration in structures of the olfactory tract.

## Methods

This study is a prospective, multicenter observational study. The study was approved by the local Ethics Committee (approval no. 22-10501-BO). In preparing this manuscript, we have used the Strengthening the Reporting of Observational Studies in Epidemiology (STROBE) Statement Checklist as a guide (see supplementary material). The study is conducted in accordance with the Declaration of Helsinki and national regulations.

### Study cohort

The study will enroll 128 participants (64 glioblastoma patients and 64 controls). Glioblastoma patients will be stratified at their first visit after radiotherapy based on extent of resection, MGMT promoter methylation status, initial olfactory test results, MRI findings of olfactory tract involvement, age, and KPS. This approach ensures balanced distribution between normosmia and hyposmia groups. Patients who cannot be assigned to either group will be excluded from further participation. Stratification will occur once post-radiochemotherapy MRI results are available, typically at visit 1 (see Table 1). The controls should essentially match the age and gender of the patients.

**Table 1 Tab1:** Overview of the planned study visits and their contents

	Screening	Baseline	Visit 1	Visit 2	Visit 3	Visit 4	Follow up visits
Signing Informed consent	x						
Verfication of inclusion and exclusion criteria	x	x					
Stratification			x				
Medical history (including cold symptoms)	x	x	x	x	x	x	x
Physical exam		x	x	x	x	x	x
Karnofsky Performance Status Scale	x	x	x	x	x	x	x
Evaluation of progression and survival data		x	x	x	x	x	x
QoL: EORTC QLQ-C30 and EORTC QLQ-BN20		x	x	x	x	x	x
Recording (severe) adverse events grade III/IV according to CTCAE V5.0		x	x	x	x	x	x
Neurocognitive testing (+ Minimal Mental Status Test)		x	x		x	x	x
Laboratory tests		x	x	x	x	x	x
Olfactory testing	x	x	x	x	x	x	x
MRI	x		x	x	x	x	x
FET PET MRI (if indicated in clinical routine)	x	x	x	x	x	x	x
Laboratory tests for scientific purposes (Biobank)		x	x	x	x	x	x
Next Generation Sequencing (if indicated in clincal routine)	x	x	x	x	x	x	x
Testing for aphasia	x						
Psychosomatic testing	x	x	x	x	x	x	x

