#### Stratification

Stratification will be performed once during the visit 1 (after radiotherapy), when, among other factors, the patient's MGMT promoter methylation status and group assignment (NG vs. HG) are determined. Additionally, the post-radiotherapy MRI of the skull will be assessed for infiltration of the olfactory tracts. Stratification may result in the exclusion of study participants after visit 1 (see Table 1).

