#### Sample size calculation and sampling strategy

The sample size was determined for a time-to-event analysis of Overall Survival (OS) using a Cox proportional hazards model. The calculation was based on the primary comparison between glioblastoma patients with hyposmia (defined as'cases'for the calculation) and those with normosmia (defined as'controls'). A hazard ratio (HR) of 0.43 for normosmia vs. hyposmia was used, a value derived from the multivariate analysis for OS in a specific subgroup of patients in the preceding pilot study [12]. As per the pre-specified statistical plan for this prospective trial, event rates over a two-year duration were prospectively defined at 47% for the hyposmia group and 53% for the normosmia group. With a significance level set at 5% and a statistical power of 80%, a total of 128 participants (64 glioblastoma patients and 64 healthy controls) is required to test this hypothesis. To control for key prognostic factors, patients are stratified after enrollment (at Visit 1) based on MGMT promoter methylation, KPS, age, extent of resection and MRI findings of olfactory tract infiltration. These variables, along with olfactory function, will be included as covariates in the final multivariate Cox proportional hazards model to adjust for potential confounding and assess the independent prognostic value of olfaction.

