### Perspective

This prospective, multicenter observational study aims to clarify the prognostic significance and underlying mechanisms of olfactory dysfunction in newly diagnosed glioblastoma. Previous retrospective data have suggested an association between impaired olfaction and reduced survival in glioblastoma patients [12], but those findings were limited by potential confounders and lacked longitudinal follow-up. This study was designed to overcome these limitations by integrating rigorous stratification, serial olfactory testing, multimodal imaging, neurocognitive assessments, and molecular profiling.

The primary objective is to determine whether olfactory dysfunction independently predicts overall survival when accounting for established prognostic factors such as MGMT promoter methylation, KPS, age, and extent of resection. In parallel, two mechanistic hypotheses are tested: (1) direct tumor invasion of olfactory-related structures, and (2) neurotoxicity resulting from radiotherapy or chemotherapy. The aim is to prove that an olfactory dysfunction in glioblastoma is intrinsic to the disease and is not caused by radiochemotherapy or local tumor infiltration in the olfactory tract.

To assess structural involvement, high-resolution coronal T2-weighted MRI and DTI are employed to detect infiltration of primary and secondary olfactory regions. Metabolic activity in these areas is further evaluated using FET PET in clinically indicated cases. These imaging data are assessed independently by two neuroradiologists to ensure objective interpretation.

To investigate treatment-related neurotoxicity, olfactory function is longitudinally monitored over two years using both identification and threshold components of the Sniffin’ Sticks test. These data are complemented by repeated neurocognitive testing, and quality of life assessments, allowing for correlation between sensory decline, cognitive function, and psychosocial burden.

The study incorporates matched healthy controls to provide normative data and differentiate disease-specific patterns from age-related olfactory decline. Additionally, tumor genome sequencing and biobanking enable exploratory analyses of molecular correlates of hyposmia and clinical outcome.

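### The described stratification does not ensure balance between the smell groups: smell status is measured, strata are formed after enrolment, and no matching rule is given

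*Protocol article*

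**What the plan says.** The Study cohort section stratifies glioblastoma patients at visit 1, after radiotherapy, "based on extent of resection, MGMT promoter methylation status, initial olfactory test results, MRI findings of olfactory tract involvement, age, and KPS". It then concludes: "This approach ensures balanced distribution between normosmia and hyposmia groups". The abstract gives the same six factors: "Patients are stratified by extent of resection, O6-Methylguanine-DNA Methyltransferase promoter methylation, radiographic involvement of olfactory regions, baseline olfactory status, age, and Karnofsky performance status". The sample size section gives five, without the smell result: "patients are stratified after enrollment (at Visit 1) based on MGMT promoter methylation, KPS, age, extent of resection and MRI findings of olfactory tract infiltration".

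Two sentences attach exclusions to this step. Study cohort: "Patients who cannot be assigned to either group will be excluded from further participation". Stratification: "Stratification may result in the exclusion of study participants after visit 1".

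The Methods section calls the study observational. The olfactory testing section sets the smell group by score: 10 or above is normosmia, below 10 is hyposmia. The Perspective section presents the step as an answer to the earlier study's weaknesses: "This study was designed to overcome these limitations by integrating rigorous stratification". The sample size section also promises to enter the stratification variables, with olfactory function, in the Cox model. The Statistics section lists the Cox covariates without extent of resection.

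**The concern.** Stratification balances groups when patients are allocated within strata. Here nobody is allocated: each patient arrives with a smell score, and sorting patients into strata afterwards leaves the age, KPS, MGMT, resection and MRI distributions of the two groups as they were. Only dropping or reweighting patients can change them. Nor can the variable that defines the groups also be a factor on which those groups are balanced.

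This matters because the Introduction reports that in the earlier study the hyposmia group was older, had less MGMT promoter methylation and a lower KPS, and that readers criticised this. If the new study reports its groups as balanced by design, readers may trust the olfaction hazard ratio for a reason that does not apply. The protection actually described is covariate adjustment.

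**Working it through.** **Figure to reproduce.** The plan states no cell count, balance criterion or number to be excluded. Its only relevant figure is 64 glioblastoma patients.

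**Inputs.** From the article: 64 patients; five factors apart from smell; a smell split of 34:39 in the earlier study (34/73 = 46.6%), which gives about 30:34 of 64. Assumed, because the article gives no levels or cut-points: two levels per factor, independent factors, prevalences all 50% or mixed 30-50%, and no association between smell and any factor.

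**Cells.**
- Five binary factors: 2^5 = 32 cells, 64/32 = 2 patients per cell.
- With smell as a sixth: 2^6 = 64 cells, 64/64 = 1 patient per cell.
- With three levels for age and for resection: 3 × 3 × 2 × 2 × 2 = 72 cells, 64/72 = 0.89 per cell.

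**Balance with nobody excluded.** For one factor at 50% prevalence, the standard deviation of the difference in proportions is √[0.25 × (1/30 + 1/34)] = 0.125. A gap of 0.20 is 0.20/0.125 = 1.60 standard deviations, so the two-sided probability is about 0.11. For five independent factors, 1 − (1 − 0.11)^5 = 0.44. Simulation (20,000 runs) agrees:

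| Prevalences | At least one gap ≥ 10 points | At least one gap ≥ 20 points |
|---|---|---|
| all 50% | 92% | 43% |
| mixed 30-50% | 92% | 40% |

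In the same runs 52-53% of occupied cells held one smell group only. This is the no-association case; if hyposmic patients again tend to be older with lower KPS, gaps would tend to be larger.

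**Balance by exclusion.** Every score is either at least 10 or below 10, so the smell score alone leaves no tested patient unassignable. The exclusion sentences may therefore be meant as matching or restriction. The cost depends on the rule:

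| Rule (assumed; none is stated) | Patients kept of 64, mean (95% range) |
|---|---|
| Exact 1:1 within the 32 cells, all 50% | 31 (22-40) |
| Exact 1:1 within the 32 cells, mixed | 33 (24-42) |
| Each factor within 10 points, stepwise exclusion | 57 (49-64) |
| Each factor within 5 points, stepwise exclusion | 55 (46-62) |

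The last two rows assume prevalences of 40-50%.

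**What exact matching would cost in power.** Take the article's two event rates at their average of 50% and its hazard ratio of 0.43. Two-sided Schoenfeld power is Φ(½√d × |ln 0.43| − 1.96), with d events. For 64 patients, d = 32: Φ(2.39 − 1.96) = 67%. For 31 to 33 patients, d is about 15.4 to 16.5, and power is 38-40%. That 64 patients give less than the stated 80% is a separate matter; the comparison here is only between keeping all 64 and keeping about half.

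**The case against.** The strongest reply is that the exclusion sentences supply the mechanism. Restriction and frequency matching are recognised ways to balance groups that were not assigned, and balance on each factor separately does not need full joint cells. The stepwise figures show that about 55 to 57 of 64 patients might suffice. This stands, and it rules out a stronger reading that is tempting: that balance cannot exist in this study, or that the groups will be unbalanced. The documents do not support that. Balance could arise by chance or through an exclusion rule not described in the article. Cells of one or two patients also depend on two levels per factor, which the article does not state.

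The reply does not rescue the word used. The article excludes those who cannot be placed in a smell group, not those without a match, and it states no quota, cut-point, tolerance or allowance for lost patients.

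A second reply is that the Cox model already adjusts for the same factors, so the main estimate does not rest on the balance claim. That is largely right and limits the consequence. A reader might infer that the olfaction hazard ratio will be biased; the documents do not show this. What remains is a guarantee the procedure does not give, an exclusion step without a stated rule, and a covariate list that differs between two sections.

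**Conclusion.** The point holds in a limited form. Balance between the smell groups is not ensured by the procedure described, and the article should not say that it is. With two-level, independent factors unrelated to smell and nobody excluded, the chance of a gap of 20 points or more on at least one of five factors is about 40-45%. If the exclusions are meant to force balance, the loss runs from a few patients under loose marginal matching to about half under exact cell matching, with no allowance for either in the 64. The listing of smell status as a stratifier, in the abstract and Study cohort but not in the sample size section, is an inconsistency that rests on no assumption. Confounding control, as written, comes from the Cox model. The change should be made, but the primary analysis does not fail without it.

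**What to change.** 1. Delete the statement that stratification ensures balance, and stop presenting rigorous stratification as the remedy for confounding in the Perspective section.
2. Remove smell status from the stratification factors in the abstract and Study cohort, in line with the sample size section.
3. Do not exclude patients after visit 1 to achieve balance, and reword the two exclusion sentences accordingly.
4. State that confounding control rests on the Cox model with all five factors: MGMT promoter methylation, KPS, age, extent of resection and MRI olfactory tract involvement. Reconcile the Statistics section, which omits extent of resection, with the sample size section.
5. Report standardised differences between the smell groups for the five factors.
6. Add one sensitivity analysis with overlap weights from a logistic propensity score on the five factors. This gives exact mean balance on the modelled terms without dropping anyone.

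The cost is wording and one extra analysis on data already collected; the article plans enrolment until December 2026, so the change can still be made. The downside is some precision in the weighted analysis: an effective sample of about 52-54 of 64 under assumed associations between smell and the factors. The weighting handles only the measured factors, as the Cox model does, so it checks the adjustment and does not protect against unmeasured confounding.

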### Study procedures

#### Study visits

Study visits for glioblastoma patients will be scheduled as follows: screening (postoperative, once histology is available), baseline (as soon as MGMT promoter methylation status is determined, but before radiotherapy), visit 1 (4 ± 1 weeks after radiotherapy ends and before adjuvant chemotherapy begins), visit 2 (3 months ± 2 weeks after end of radiotherapy), visit 3 (6 months ± 2 weeks after end of radiotherapy), visit 4 (12 months ± 2 weeks after end of radiotherapy), and follow-up visits (every 6 months ± 2 weeks after visit 4, for a maximum of 2 years).

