#### Obtaining informed consent

Informed consent will be obtained during the screening visit.

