#### Investigation of the olfactory sense

The extended Burghart test comprises a threshold and an identification module for detailed olfactory assessment [11]. The threshold test includes 16 dilutions of an odorant (plus blanks), presented in triplets; correct and incorrect choices guide up- or downgrading the dilution level until a consistent threshold is found (score range 1–16). Higher scores indicate a better ability to detect weak odors. The identification test features 16 possible smells, with 12 randomly selected at each test; participants choose the correct smell from four options. Each correct answer scores 1 point (maximum 12). Testing each nostril separately, average scores ≥ 10 classify as normosmia, < 10 as hyposmia.

During screening, only the identification test is performed to assign participants to the normosmia or hyposmia group. At subsequent visits, both threshold and identification modules are done. The threshold test is carried out with both nostrils simultaneously, starting at dilution 16. Participants must avoid eating, drinking, smoking, or chewing gum for at least 15 min before testing. Correct answers are not revealed to maintain test reliability across repeated assessments.

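### Consented, eligible patients can be excluded after visit 1 under an undefined balancing rule that the planned adjustment makes unnecessary; the cost is in patients, power and generalisability, and possibly in bias

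*Protocol article*

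**What the plan says.** Consent comes early: "Informed consent will be obtained during the screening visit", which takes place after surgery and before radiotherapy. Table 1 checks eligibility only at screening and baseline.

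Stratification comes later, at "visit 1 (4 ± 1 weeks after radiotherapy ends and before adjuvant chemotherapy begins". Study cohort lists the items used: extent of resection, MGMT status, initial olfactory result, MRI findings, age and KPS. The Stratification section adds: "Additionally, the post-radiotherapy MRI of the skull will be assessed for infiltration of the olfactory tracts". The stated purpose is balance: "This approach ensures balanced distribution between normosmia and hyposmia groups".

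Two sections give the consequence for patients who do not fit. Study cohort: "Patients who cannot be assigned to either group will be excluded from further participation". Stratification: "Stratification may result in the exclusion of study participants after visit 1". Neither defines what makes a patient unassignable.

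The olfactory class has two categories: "average scores ≥ 10 classify as normosmia, < 10 as hyposmia". The section on investigating the olfactory sense assigns it from the identification test at screening, whereas the Stratification section says that group assignment is determined at visit 1.

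The sample-size section says that the stratification factors, extent of resection included, will be covariates in the final Cox model. The Statistics section lists MGMT, KPS, age, MRI findings and olfactory function, without extent of resection.

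**The concern.** The study asks whether olfaction measured before radiotherapy predicts survival in newly diagnosed glioblastoma. Such a cohort should be defined by what is known when the marker is measured. Here, staying in the study depends on a decision taken after radiotherapy, under an unstated rule that draws partly on information arising after the marker was measured.

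Three things are at stake. The result may describe only patients who reach visit 1. Patients and deaths may be discarded from a small study with no stated allowance. And if exclusion is related to prognosis in a way the model does not capture, the hazard ratio for olfaction can be wrong.

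**Working it through.** **1. Where can exclusion come from?** The cut-off at 10 leaves no third category, and the test is done at screening. A patient without a usable test would be recognised then, not after visit 1. MGMT status is available by baseline, because the Study visits section times baseline by it. Age and extent of resection are also known before radiotherapy. What visit 1 adds is the post-radiotherapy MRI and possibly a later KPS. Exclusion at that point therefore rests on failing to fit the balance scheme or on lacking visit-1 data.

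**2. Can it ensure balance?** Besides olfaction there are five factors. Even if each is cut in two (an assumption), there are 2^5 = 32 cells, against about 64/2 = 32 patients per group: on average one per cell. Balance on all five cannot be guaranteed.

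**3. The plan's sample size.** Inputs from the sample-size section: HR 0.43, 5% significance (taken as two-sided), 80% power, two-year event rates of 47% and 53% (mean 50%). Equal groups are assumed.

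- Events = 4(1.960 + 0.842)² / (ln 0.43)² = 31.40/0.712 = 44.1, so 45 events and 45/0.50 = 90 patients. One-sided, it is 35 events and 70 patients. Neither gives 64; that is a separate fault.
- Power = Φ(√D/2 × 0.844 − 1.960), with D the number of deaths.

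| Assumed exclusion | Patients | Deaths at 50% | Power |
|---|---|---|---|
| 0% | 64 | 32.0 | 66.5% |
| 10% | 57.6 | 28.8 | 62.0% |
| 20% | 51.2 | 25.6 | 57.0% |
| 30% | 44.8 | 22.4 | 51.5% |

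The article gives no exclusion rate, so the first column is a range. Keeping 64 analysable patients would need 64/0.9, rounded up to 72, or 64/0.8 = 80 enrolled.

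**4. Deaths before visit 1.** Assume 2.5 to 4.5 months from time origin to visit 1 and exponential survival at the pilot medians in the Introduction (20.9 and 40.6 months).

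- Hyposmia: 1 − 0.5^(2.5/20.9) = 8.0%, to 1 − 0.5^(4.5/20.9) = 13.9%
- Normosmia: 1 − 0.5^(2.5/40.6) = 4.2%, to 1 − 0.5^(4.5/40.6) = 7.4%

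With 32 per group this is 2.5 to 4.4 plus 1.3 to 2.4, or about 4 to 7 deaths in all.

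**5. Effect on the hazard ratio.** A simulated cohort of 200,000 used a true HR of 0.43, 47% hyposmic, one measured prognostic factor in the model, and unmeasured log-normal frailty of the stated SD. Compare within columns, since frailty itself moves the full-cohort value. Rows 3 to 5 also require survival to 3.5 months.

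| Analysed | SD 0 | SD 0.5 | SD 1.0 |
|---|---|---|---|
| All patients | 0.426 | 0.458 | 0.520 |
| Visit-1 survivors only | 0.425 | 0.462–0.466 | 0.536–0.544 |
| 24–27% removed, mainly to balance the measured factor | 0.423 | 0.461 | 0.537 |
| Worst 10–20% of hyposmic patients removed, by unmeasured prognosis | – | 0.502–0.538 | 0.590–0.662 |
| Worst 10–20% of both groups removed | – | 0.450–0.444 | 0.499–0.475 |

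If the factor used for balancing is left out of the model (SD 0), the estimate is 0.373 in all patients and 0.464 after the exclusions, on either side of the adjusted 0.426. Extent of resection would be in that position under the Statistics section's covariate list.

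**The case against.** A reader might infer that the rule biases the hazard ratio towards 1, because more early deaths are expected in hyposmia and these are lost. The documents do not support that as a certainty. Under the planned proportional-hazards model, losing early deaths leaves the hazard ratio essentially where it was (0.426 against 0.425) and shifts it modestly with frailty. Larger shifts need exclusion tied to unmeasured or unadjusted prognosis. They can go either way, and no section says that this happens.

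A reader might also infer exact matching on five binary factors, which in simulation keeps only about 29 to 33 of 64 patients and, with about 16 events, gives roughly 39% power. No section describes matching patients to each other or dichotomising age and KPS, so those figures do not describe this plan.

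Other reservations stand in part. The text does not say that patients who die before visit 1 leave the survival analysis; Table 1 records survival from baseline, and the time origin and analysis set may be defined in a document not shown. Progression does not prevent stratification, since the MRI is routine. Excluded patients may be replaced. The pilot medians come from patients tested at various times, only 15 of them before chemoradiotherapy, so step 4 is illustrative. Most of the gap between 66.5% and 80% power exists before anyone is excluded.

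None of this removes the stated rule, which takes consented and eligible patients out after visit 1 without a definition.

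**Conclusion.** The point holds as a design fault. The rule is undefined, operates after the marker is measured and cannot ensure balance on five factors with about 32 patients per group. It adds nothing to confounding control that covariate adjustment does not already give.

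The costs differ in certainty. If the analysis follows the exclusions, absolute survival and generalisability to newly diagnosed glioblastoma are distorted; under the assumptions in step 4, 8–14% of hyposmic and 4–7% of normosmic patients would not reach visit 1. If exclusions are not replaced, each 10% costs about 4.5 to 5.5 percentage points of power, from a starting value of 66.5%. Bias in the hazard ratio is possible, but its size and direction cannot be derived from the article. The most concrete route is extent of resection, which is used for stratification but missing from the Statistics section's model.

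**What to change.** 1. Delete the exclusion after visit 1.
2. Set the olfactory group from the pre-radiotherapy identification test, and reconcile the Stratification section with the section on investigating the olfactory sense.
3. Keep every eligible patient with that test in the primary overall-survival analysis, from a pre-radiotherapy time zero, whatever happens at visit 1.
4. Control imbalance by covariate adjustment including extent of resection, and reconcile the Statistics section with the sample-size section.
5. For olfactory-tract involvement in the primary model, use the postoperative MRI where it is adequate for the assessment, or impute missing values. The post-radiotherapy finding is unavailable for early deaths; requiring it would drop them again, and using it as a fixed covariate from an earlier time zero conditions on later information. Analyse that finding in a secondary landmark analysis starting at visit 1.
6. Recover vital status, where consent allows, for patients already excluded, and report the number of and reasons for exclusions.

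The cost is a protocol amendment, a little more follow-up, less exact group balance and a less precise MRI covariate in the primary model. With 32 patients recruited by April 2025 and enrolment planned to December 2026, there is still time.
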